# Electromagnetic guided bedside or endoscopic placement of nasoenteral feeding tubes in surgical patients (CORE trial): study protocol for a randomized controlled trial

**DOI:** 10.1186/s13063-015-0633-1

**Published:** 2015-03-26

**Keywords:** Nasoenteral feeding, Post-pyloric feeding, Feeding tubes, Enteral feeding, Enteral nutrition, Electromagnetic guidance, Endoscopy, Surgery, Gastroparesis

## Abstract

**Background:**

Gastroparesis is common in surgical patients and frequently leads to the need for enteral tube feeding. Nasoenteral feeding tubes are usually placed endoscopically by gastroenterologists, but this procedure is relatively cumbersome for patients and labor-intensive for hospital staff. Electromagnetic (EM) guided bedside placement of nasoenteral feeding tubes by nurses may reduce patient discomfort, workload and costs, but randomized studies are lacking, especially in surgical patients. We hypothesize that EM guided bedside placement of nasoenteral feeding tubes is at least as effective as endoscopic placement in surgical patients, at lower costs.

**Methods/Design:**

The CORE trial is an investigator-initiated, parallel-group, pragmatic, multicenter randomized controlled non-inferiority trial. A total of 154 patients admitted to gastrointestinal surgical wards in five hospitals, requiring nasoenteral feeding, will be randomly allocated to undergo EM guided or endoscopic nasoenteral feeding tube placement. Primary outcome is reinsertion of the feeding tube, defined as the insertion of an endoscope or tube in the nose/mouth and esophagus for (re)placement of the feeding tube (e.g. after failed initial placement or dislodgement or blockage of the tube). Secondary outcomes include patient-reported outcomes, costs and tube (placement) related complications.

**Discussion:**

The CORE trial is designed to generate evidence on the effectiveness of EM guided placement of nasoenteral feeding tubes in surgical patients and the impact on costs as compared to endoscopic placement. The trial potentially offers a strong argument for wider implementation of this technique as method of choice for placement of nasoenteral feeding tubes.

**Trial registration:**

Dutch Trial Register: NTR4420, date registered 5-feb-2014

**Electronic supplementary material:**

The online version of this article (doi:10.1186/s13063-015-0633-1) contains supplementary material, which is available to authorized users.

## Background

Gastroparesis, or delayed gastric emptying, occurs in approximately 2% of surgical patients [1,2]. It is caused by the disease itself, an operation, postoperative complications such as intra-abdominal infection, or concomitant underlying diseases such as diabetes. Patients suffering from gastroparesis do not tolerate a normal diet and may eventually become malnourished, which negatively affects clinical outcomes [3-5]. Therefore, in patients who are not able to achieve at least 50% of their daily required caloric intake for several consecutive days, it is common practice to place a nasoenteral feeding tube to deliver enteral nutrition. Parenteral nutrition is only used when enteral nutrition is contraindicated, not feasible or not sufficient in delivering nutrient needs, as parenteral nutrition has shown to be associated with an increase in infectious complications and higher costs [6].

Nasoenteral feeding tube placement can be challenging, especially in patients with gastroparesis. Blind placement is usually unsuccessful and may lead to complications such as pneumothorax and pneumonia due to inadvertent placement in the bronchus in over 2% of placement attempts [7].

Therefore, nasoenteral feeding tubes are usually placed endoscopically, regularly followed by abdominal radiography to confirm a correct position of the tube. Endoscopic feeding tube placement requires fasting and patient transportation between the clinical ward, endoscopy and radiology departments. The procedure is also relatively expensive as it has to be performed by a gastroenterologist and one or two endoscopy nurses.

Hence, both patients and hospital staff perceive endoscopic tube placement as uncomfortable and cumbersome. Furthermore, patients may need several repeated procedures during hospital admission. We noticed a 34% dislodgement rate of nasoenteral feeding tubes within the first week after placement [8]. Some 50% of these dislodged tubes require replacement, which not only leads to additional discomfort for the patient and temporary decrease in caloric intake, but also to an increased workload for nursing and medical staff, and additional costs.

Electromagnetic (EM) guided placement of nasoenteral feeding tubes is suggested to be less discomforting to the patient and seems cost-saving compared with endoscopy, as it can be performed on the clinical ward at the patient’s bedside by a specialized nurse. Confirmation of the tube’s position on an abdominal radiograph is unnecessary and repositioning of a tube that has dislodged into the stomach can be done with the stylet without the need for a fully repeated procedure [9-12]. Implementation of this technique requires training of nurses (e.g. a full-day training session, ideally followed by a number of supervised placement procedures) and purchasing the equipment ($ 7925) [10,13].

A recent systematic review by our group showed that EM guided tube placement in adult patients is not inferior to endoscopic placement regarding efficacy and safety in patients with normal upper gastrointestinal (GI) anatomy [14]. Success rates were similar and only minor complications such as epistaxis and dislodgement or blockage of the tube were reported. However, the available evidence is of moderate quality and lacks data on patient-reported outcomes and costs. Moreover, studies in surgical patients, especially those with an altered upper GI anatomy after surgery, are scarce. In our previous retrospective cohort study, EM guided placement was successful in 58% of patients with an altered upper GI anatomy, which seems low, but may be acceptable given the potential benefits for the patient [15]. A well-designed pragmatic, multicenter, randomized controlled trial is therefore needed to assess the true effectiveness and benefits of EM guided nasoenteral feeding tube placement in the surgical population.

The aim of the CORE trial is to determine the effectiveness of EM guided bedside placement as compared to endoscopic placement of a nasoenteral feeding tube in surgical patients requiring nasoenteral feeding.

## Methods

### Design

The CORE trial is an investigator-initiated, parallel-group, pragmatic, multicenter, randomized controlled non-inferiority trial. Patients will be randomly allocated to undergo EM guided or endoscopic nasoenteral feeding tube placement.

### Study population

All adult patients admitted to the gastrointestinal surgical wards in one of the five participating centers with an indication for post-pyloric enteral nutrition will be assessed for eligibility, regardless of the reason for admission (e.g. surgical procedures or conditions not requiring surgery).

### Inclusion criteria

Inclusion criteria are: admission to a gastrointestinal surgical ward; need for post-pyloric enteral nutrition via nasoenteral feeding tube as indicated by the treating physician and/or consulting dietitian (e.g. because of severe gastroparesis/gastric stasis not responding to prokinetics, intolerance of oral feeding due to gastroduodenal inflammation, postprandial pain or passage disorder due to swelling or outside pressure onto the duodenum or proximal enteric fistulae); and written informed consent.

### Exclusion criteria

Exclusion criteria are: age < 18 years; presence of a contraindication for enteral feeding; presence of a contraindication for EM guided placement (i.e. a history of esophageal varices, upper GI stenosis or obstruction, recent (<30 days) esophagectomy, or the presence of an implanted medical device that may be affected by the electromagnetic field of the EM guided system or vice versa (except for pacemakers and defibrillators) and necessity for tube placement during weekends or holidays.

### Randomization

Eligible patients will be recruited on the clinical ward by the principal investigators or a designated substitute. After obtaining informed consent, patients will be randomized centrally by the study coordinator using an online randomization module (Clinical Research Unit, Academic Medical Center, Amsterdam, the Netherlands) in a 1:1 ratio between EM guided and endoscopic tube placement (Figure 1).

**Figure 1 Fig1:**
[figure not shown]
**Flow chart of participants in the CORE trial according to CONSORT.**

Randomization will be stratified by center to balance differences in general treatment regimens between hospitals and according to the presence of an altered upper GI (esophageal, gastric or duodenal) anatomy after previous surgery. Randomization is balanced for the presence of an altered upper GI anatomy because an altered anatomy might hamper feeding tube placement and decrease success rates. Permuted-block allocation is used to provide treatment allocation in equal proportions. The block size will be subject to random variation and concealed to all investigators involved in the study.

Blinding of patients and caregivers was considered practically unfeasible given the obvious differences between the two methods of tube placement (e.g. bedside placement or placement in the endoscopy department). Moreover, the primary outcome (reinsertion of an endoscope of tube) is sufficiently objective to minimize any potential risk of measurement bias. Feeding tubes are reinserted when oral intake is less than 50% of the patient’s daily required caloric intake. This decision will be made by the treating physician, whenever possible after consulting a dietitian.

### Group A: Electromagnetic guided nasoenteral feeding tube placement

The feeding tube (Corflo® nasojejunal feeding tube, Corpak Medsystems, Wheeling, Ill, US) is placed by a trained nurse at the patient’s bedside on the clinical ward, with the patient in a supine position. If a nasogastric decompression tube is in place, it is advised, but not mandatory, to empty the stomach and remove the nasogastric tube before proceeding. Preprocedural fasting is not required. By using an electromagnetic transmitting stylet, the nurse can follow the path of the tip of the feeding tube on a monitor screen (Cortrak® Enteral Access System, Corpak Medsystems, Wheeling, Ill, US) (Figure 2). The stylet at the tip of the feeding tube transmits its signal to a receiver unit placed at the patient’s epigastric region. Both the stylet and the receiver unit are attached by a cable to the monitor unit, which provides a graphic display of the feeding tube tip location and the followed track. In the anterior view, the tube can be followed on its way through the esophagus, stomach, duodenum, and jejunum. In the depth cross-section, the passage of the tube from the pylorus into the duodenal bulb and the second part of the duodenum can be seen. The tube is advanced to a post-pyloric position, preferably near or beyond the duodenojejunal flexure. Adequate positioning is assessed by the path of the tube on the screen. Subsequently, the transmitting stylet is removed from the feeding tube. Finally, the tube is secured to the nostrils with tape. Abdominal radiographs are not used, as the Cortrak® Enteral Access System was shown to correlate with abdominal radiography in 99.5% of cases and is cleared by the Food and Drug Administration (FDA) for feeding tube placement confirmation [9,11]. The stylet is kept at the patient’s bedside in case repositioning of the nasoenteral tube is required. The procedure is abandoned if the tip of the tube has not passed the pylorus after 30 minutes. In case of failure of EM guided placement, patients allocated to EM guided bedside placement will undergo endoscopic placement. According to the intention-to-treat principles these patients will be analyzed in the EM guided group.

**Figure 2 Fig2:**
[figure not shown]
**The Cortrak® Enteral Access System (electromagnetic transmitting stylet, receiver unit and enteral feeding tube).** The tip of the tube is displayed on the monitor as a red dot and a yellow line reflects the path of the tube. *Image reproduced with permission of CORPAK MedSystems.*

### Group B: Endoscopic nasoenteral feeding tube placement

Endoscopy is performed by trained gastroenterologists (or supervised gastroenterologists in training) assisted by one or two endoscopy nurses in the endoscopy department. Patients fast from midnight but clear fluids are allowed up to 3 hours before the procedure. Conscious sedation is used if indicated (e.g. requested by the patient). A nasal or oral endoscope is introduced into the duodenum or jejunum. According to the gastroenterologist’s preference, the feeding tube is either pulled along with the endoscope, advanced through the endoscope or advanced over a guide wire and placed as far as possible in the duodenum or jejunum. Finally, the tube is secured to the nostrils with tape. Within 3 hours after tube placement, an abdominal radiograph is performed and reviewed by an independent radiologist who is not involved in the study. In case of incorrect feeding tube placement, repeat endoscopic tube placement is performed. In case of second placement failure, the study is terminated for that patient and an alternative feeding strategy (but not EM guided placement) is used according to the preference of the treating physician.

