### Primary outcome

The primary outcome is the need for reinsertion of the feeding tube, defined as the insertion of an endoscope or tube in the nose/mouth and esophagus for (re)placement of the feeding tube. This outcome reflects the feasibility of the technique itself as well as the need for repeated procedures due to tube-related complications. Tubes will be reinserted when there is an ongoing indication for enteral feeding (as advised by the consulting dietitian) after initial unsuccessful placement, dislodgement or blockage of the tube. Endoscopic placement after failed initial EM guided attempt (crossover) is also considered a reinsertion. Repositioning guided by the EM transmitting stylet is not considered a reinsertion as long as the tube has not left the stomach/esophagus.

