**CORE trial flow chart of eligibility and group allocation.**

Patients will be asked to complete a short questionnaire after each tube (re)placement procedure. The questionnaire will consist of a visual analogue scale (VAS) scoring sheet, for the dimensions discomfort, pain, social embarrassment, anxiety, and total burden (comparable to the study by Deutekom *et al*. [16]). In addition, patients will also be asked what their advice would be to a friend or colleague in the same situation. Patients randomized to EM guided tube placement with past experiences with endoscopic tube placement and vice versa will additionally be asked for their preference for one or the other tube placement method.

Patients are followed for as long as they are hospitalized and during any outpatient clinic or day-care visit related to the feeding tube (see Additional file 1 for the time schedule of enrolment, interventions, and assessments).

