#### Analyses

All analyses will be according to the intention-to-treat principles, meaning that all randomized patients are included in their initially assigned study arm, regardless of adherence to study protocol. The primary and secondary outcomes will be compared between the treatment groups. Results are presented as risk ratios with corresponding 95% confidence intervals. Except for the primary analysis of non-inferiority, a difference with a two-tailed P < 0.05 is considered statistically significant. In the event of imbalance between the two study arms a multivariable logistic regression will be used to correct for possible confounders. Additional as-treated and per-protocol analyses will be performed for the primary endpoint and the success rate of both tube placement methods.

A predefined subgroup analysis will be performed in patients with and without an altered upper GI anatomy after previous surgery. We will use logistic regression models to perform a formal test for interaction to assess whether outcomes differed significantly between these subgroups.

Interim analysis to evaluate serious adverse events and potentially prematurely terminate the study will not be performed, because of the perceived negligible risk associated with participation in this study.

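### Ending the study for endoscopy patients after a second failed placement conflicts with follow-up to discharge and could lose their later secondary outcomes and costs

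*Protocol article*

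**What the plan says.** The Group B section of the protocol article sets out two steps after a failed endoscopic placement. First: "In case of incorrect feeding tube placement, repeat endoscopic tube placement is performed". Then: "In case of second placement failure, the study is terminated for that patient and an alternative feeding strategy (but not EM guided placement) is used", the choice of strategy resting with the treating physician.

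The Group A section handles failure differently: "In case of failure of EM guided placement, patients allocated to EM guided bedside placement will undergo endoscopic placement". It adds: "According to the intention-to-treat principles these patients will be analyzed in the EM guided group". It does not say what happens to study participation if that endoscopy fails too.

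Follow-up is described once, for both arms and without exception, under Data collection and follow-up: "Patients are followed for as long as they are hospitalized". Outpatient and day-care visits for the tube are also covered. The Analyses section defines intention to treat so that "all randomized patients are included in their initially assigned study arm, regardless of adherence to study protocol".

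**The concern.** A sentence that ends the study for a patient and a sentence that follows every patient to discharge cannot both be carried out literally for the same patient. The sentence that ends the study applies only after treatment failure and is stated only for the endoscopy arm. If sites act on it, follow-up would stop because of the outcome of treatment, in one arm, for the patients in whom endoscopic placement went worst.

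Much of what the Secondary outcomes section lists arises after that moment: parenteral nutrition, further feeding-related interventions, complications, length of stay, and the costs attached to them. The replacement feeding strategy that the rule itself triggers would go uncounted. Cost is not a side issue, since the hypothesis in the abstract pairs effectiveness with lower costs for EM placement. Case report forms are completed by local physicians or the study coordinator across five hospitals, so the sentence may be read in more than one way.

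**Working it through.** **1. The plan's own figure.** Inputs from Sample size calculation: success 70% (endoscopy) and 78% (EM), margin 10 points, significance level 0.05, power 80%, loss 5%. With the level used one-sided:

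- n per arm = (1.645 + 0.842)² × (0.70×0.30 + 0.78×0.22) / (0.10 + 0.08)² = 6.18 × 0.3816 / 0.0324 = 72.8, so 73.
- 73 / 0.95 = 76.8, so 77 per arm and 154 in total.

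Both stated figures are reproduced. Power at 73 per arm is 80.1%.

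**2. Does the rule touch the primary outcome?** A reinsertion is "defined as the insertion of an endoscope or tube in the nose/mouth and esophagus for (re)placement of the feeding tube". The Primary outcome section includes reinsertion after an unsuccessful first placement. A second failure requires a second placement attempt, and that attempt is itself a reinsertion. So every patient to whom the rule applies has already had the primary event. Kept as events, they leave endoscopy success at 70% and power at 80.1%. Success of the first placement and the questionnaire after it also precede the rule.

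**3. What lies after the rule.** Setting the sections side by side:

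- Group B: the study ends for the patient at the second failure.
- Data collection and follow-up: the patient is followed to discharge, with no exception.
- Group A: a failed EM patient goes on to endoscopy and is analyzed in the EM group; no end of study is stated.
- Secondary outcomes: parenteral nutrition, feeding-related interventions, complications, length of stay and costs can all arise after the second failure.
- Safety: all deaths are to be reported in any case, so mortality is less exposed than the rest.

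**4. How many patients?** The document gives no endoscopic failure rate, so the following rests on assumption. Let the first placement fail in 5% to 30% of patients, and the second fail in 10% to 50% of those. The upper 30% is the most the planning figure allows, since 70% of the arm is assumed to need no reinsertion.

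- Lowest: 77 × 0.05 × 0.10 = 0.4 patients (0.5%).
- Middle: 77 × 0.10 × 0.30 = 2.3 patients (3%).
- Highest: 77 × 0.30 × 0.50 = 11.6 patients (15%).

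For comparison, the 5% loss allowance is about 77 − 73 = 4 patients per arm.

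**5. Direction.** Stopping collection early can only leave out endoscopy-arm costs, hospital days, interventions and parenteral nutrition. Recorded endoscopy burden and cost would therefore be too low, which narrows any cost advantage of EM placement.

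**The case against.** The strongest reply is that the sentence ends only study-directed tube placement. It stands in the description of the intervention, leads straight into what feeding follows, and keeps a restriction in force (no EM placement) that makes little sense for someone who has left the study. Data collection has its own section, which makes no exception. This reading is plausible and may be what was meant, but the article does not state it, so the tension between the two sections remains.

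A second reply is that the one-arm asymmetry rests partly on silence. The comparable EM patient, with failed EM placement and then failed endoscopy, is not addressed, and the full protocol may cover that case. This stands: differential follow-up is a risk of the wording, not an established fact.

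Three stronger readings are tempting and are not supported:

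- A reader might infer that these patients drop out of the non-inferiority analysis. If they did, removing 2, 4 or 8 of 73 would raise endoscopy success to 51.1/71 = 72.0%, 51.1/69 = 74.1% or 51.1/65 = 78.6%, and cut power to 71.9%, 61.8% or 37.9%. The Analyses section does not permit that exclusion.
- A reader might infer a direct contradiction of intention to treat. The Analyses section fixes who is analyzed and in which arm, and the Group B section removes nobody from the analysis. The conflict is indirect: patients can be counted in their arm and still have later outcomes missing.
- A reader might put a percentage on the cost bias. If 2% to 5% of the arm cost five times the mean and only one mean's worth were recorded, the understatement would be 0.02 × 4 = 8% to 0.05 × 4 = 20%. Neither the share nor the ratio is in the document. Nor does one mean's worth fit: two endoscopies precede the rule, while an arm in which 70% need one placement and 30% exactly two averages 0.7 × 1 + 0.3 × 2 = 1.3. Ward-stay costs are not among the cost items listed.

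**Conclusion.** The point holds as a conflict between the Group B section and the follow-up rule, with consequences for secondary outcomes only. The primary outcome, sample size and power do not change, provided that affected patients are kept as events, as the outcome definition and the Analyses section require. Parenteral nutrition, feeding-related interventions, complications, length of stay and costs could be missing for the worst endoscopy failures. The direction is clear: endoscopy would look less burdensome and cheaper than it is, which biases against the lower-cost hypothesis for EM placement.

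The size cannot be derived. The range of 0.4 to 11.6 patients in an arm of 77 reflects assumed failure rates, and no credible cost figure can be attached to it. The conclusion also depends on sites taking the sentence literally; if it ends only study-directed placement, nothing is lost and only the wording needs repair.

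**What to change.** Reconcile the Group B section with Data collection and follow-up on data collection alone. State that a second placement failure does not end study participation, that the patient counts as a primary event and stays in the assigned arm, and that all outcomes and costs are collected to the end of follow-up. Apply the same data-collection rule to EM-arm patients whose endoscopy after conversion also fails. The change should take no position on which feeding strategy follows, or on when placement attempts stop in either arm.

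The cost is a short clarification and continued completion of an existing case report form for what are probably a few inpatients. The sample size is unchanged.
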